#### 11.3.9 *Urine drug screen*

Urine will be screened for drugs of abuse at visits outlined in the schedule of events (Table 8.1-1 and Table 8.1-2) using the AlereTM Drug Screen Test Panel. Additional random tests can be performed during the study period.

#### 11.3.10 *Alcohol breath test*

An alcohol breath test will be performed at visits outlined in the schedule of events (Table 8.1-1 and Table 8.1-2). Additional random tests can be performed during the study period.

#### 11.3.11 *Baseline symptoms*

A baseline symptom is defined as an event that occurs between subject's signing of the ICF until the first administration of IMP (*i.e.* an event that occurs during the screening period).

Such events are not AEs and will be recorded as baseline symptoms in the Medical History Log in the eCRF.

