The Principal Investigator at the research clinic will ascertain that adequate facilities and procedures are available to handle emergency situations should they occur during the study. The medical staff at [REDACTED] has extensive experience from early Phase I and FIH studies and adequate procedures are in place to handle unexpected and expected adverse reactions in the study subjects. The FIH research clinic is located adjacent and on the same floor as the Intensive Care Unit (ICU) at the University Hospital in Uppsala. [REDACTED] has a separate agreement with the ICU for support in case of an emergency and has been regularly inspected by the Swedish Medical Products Agency (MPA) regarding the conduct of FIH studies.

Besides the risks related to the IMP administration as described above, there may also be risks related to the experimental induction of wounds, such as pain, bleeding and bruising. In order to reduce the pain during wound punching, subjects will be treated with local anesthetics (injected and/or topical) prior to the procedure. A brief stinging pain may occur when the local anesthetic is injected. Anaphylaxis is a possible complication associated with local anesthesia although a true type I hypersensitivity reaction to local anesthesia is very rarely seen. Any anaphylactic reaction is likely to occur prior to the IMP administration.

Bleeding is the most common complication during skin biopsy. Compression for hemostasis will hence be applied if necessary. In case of excessive bleeding (which is rare but may occur), where hemostasis is not achieved by compression, diathermy may be used. For details, refer to Section 11.4. Subjects with bleeding tendency, known bleeding disorders, or subjects who are taking blood-thinning medications such as warfarin will not be included in the study. Also, any vasoactive (constrictor or dilator) medication, prescription or over-the-counter (OTC) drugs that could modulate blood flow is disallowed from 2 weeks prior to screening and during the study. Importantly, this also includes non-steroidal anti-inflammatory drugs (NSAIDs) which are disallowed from 2 weeks prior to screening and during the whole study until Visit 6 of the SAD part and Visit 13 of the MAD part.

Damage to structures such as nerves or vessels are rarely observed complications during skin biopsy.

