#### **Treatment phase (Visit 1 to Visit 6)**

Screening (Visit 1) will take place from Day -28 to Day -1. At Visit 2, eligible subjects will be admitted to the research clinic on Day 1 for pre-dose safety assessments and full-thickness wound punching with a biopsy punch (6 mm in diameter) on the ventral aspect of the upper arms (2 wounds/arm). The wounds should be separated by approximately 4 cm. One biopsy per subject will be saved for baseline histopathology analysis using the procedure described in Section 11.8.2. Each wound will be numbered using a permanent marker. Prior to wound punching, subjects will be treated with local anesthesia (injected and/or topical) and the area will be cleaned with antiseptics (70% ethanol). The wound punching procedure will be detailed in a separate manual.

A single dose of the IMP will be topically applied to each of the wounds using a pipette; activated ILP100-DP to 2 wounds on one arm and placebo to the other 2 wounds on the other arm as randomized. There should be 1 hour ( $\pm 10\%$ ) between the last wound punch and the start of IMP application to allow for pre-dose study assessments and hemostasis. Two unblinded persons will take part of the administration process, one will perform the application of IMP and the other one will confirm that the correct treatment is administered to the intended wound, i.e. in accordance with the randomization list. The IMP administration will be documented by video recording. Each wound will be dressed separately using an adhesive, transparent film, isolating the wounds from each other. An elastic, tubular bandage will be used on top of the films. For details on the wound incision and IMP application processes, refer to Section 11.4 and Section 10.6, respectively.

The subjects will be carefully monitored by clinical staff during and after IMP administration and will remain at the research clinic for at least 4 hours after dose. Vital signs and ECG will be checked as detailed in Table 8.1-1. There is immediate access to equipment, qualified staff and an ICU in case of an acute emergency. Up to 2 subjects will be dosed on the same day.

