| Baseline symptoms                                           | X               |                           |                 |                 |                 |                                     |                     |                   |                  |                   |                      |                  |        |
| Adverse events                                              |                 | X            | X               | X               | X               | X                                   | X      | X    | X   | X    | X       | X   |        |
| Prior and concomitant medications              | X               | X                         | X               | X               | X               | X                                   | X                   | X                 | X                | X                 | X                    | X                |        |

1. Or after early withdrawal.
2. Prior to wound punching.
3. Re-check of eligibility criteria

4. Weight only.
5. Drug tests may also be performed at 1 to 2 additional random occasions during the study.
6. Females only. Screening: blood/serum tests, other visits: urine test.
7. Pre-dose and 1 and 4 hours (before the subject leaves the clinic) after dose.
8. Prior to the first IMP administration. Can be performed at screening or at any time between screening and the first IMP administration.
9. One biopsy (wound punch) should be saved for baseline histopathology analysis as described in Section 11.8.2.
10. One sample of resuspended drug product for viable count, see Section 11.6. Cohort 1 only.
11. After wound punching, prior to IMP application and 4 h post application.
12. Local tolerability assessed by the Investigator (direct observation) and by 3 to 5 independent evaluators using photographs. Day 1: after wound punching, prior to IMP application and 4 hours post application. Subjects assess local tolerability from Day 2.
13. Local tolerability during the long-term follow-up assessed by the Investigator only.
14. CXCL12 blood sampling prior to wound punching at 9:00±2 hours, 1 hour post the last wound punch (within 5 minutes of start of IMP application, which should start 1 hour (±10% post the last wound punch) and 1 hour (±10%) after the last IMP application.

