15. CXCL12 blood sampling at 9:00±2 hours. On Day 2: 24h±2 hours post dose but no later than 11:00. On Day 3 and 14, also plating of blood samples prior to centrifugation for blood culturing, see Section 11.8.1 and Section 11.8.1.2.
16. 48 hours after IMP administration (one biopsy from a CXCL12 treated wound and one from a placebo treated wound)
17. Wound healing assessed by the Investigator (direct observation) and by 3 to 5 independent evaluators using photographs.
18. Wound area assessed by 3 to 5 independent evaluators using photographs and the Image J software (National Institutes of health [NIH]) or equivalent.
19. Baseline wound area measurements based on photos taken after wound punching prior to IMP application.
20. Scar tissue formation assessed by the Investigator (direct observation) and by 3 to 5 independent experts using photographs at Visit 6. Scar tissue formation during the long-term follow-up assessed by the Investigator only. Normal/abnormal and Vancouver scar scale. One assessment per wound.
21. Dressing if indicated.
22. From administration of IMP.
23. Collection of AEs including, but not limited to, mortality, development of any new/recurrent cancer, development of infection, immunogenicity related reactions.
24. For definitions of prior and concomitant medications, see Section 11.3.6.

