#### *11.7.1.6 Time period and frequency for collecting adverse events*

AEs (including SAEs) will be collected from the start of IMP administration until the end-of-study visit. From Visit 7 and 14 in the SAD and MAD part, respectively, pre-defined AEs will be asked for.

Any AE with start date on the day of first IMP administration must be recorded with start time.

At the end-of-study visit, information on new AEs, if any, and stop dates for previously reported AEs must be recorded (if known).

Investigators are not obligated to actively seek AE or SAE after conclusion of the study participation. However, if the investigator learns of any SAE, including a death, at any time after a participant has been discharged from the study, and he/she considers the event to be reasonably related to the study intervention or study participation, the investigator must promptly notify the sponsor.

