#### *11.7.1.12 Reporting of serious adverse events*

SAE reporting should be performed by the investigator within 24 hours of awareness via the eCRF. All available information regarding the SAE should be entered in the AE Log for the specific subject. By saving the event as “serious” in the eCRF, an e-mail alert is sent to predefined recipients to highlight that an SAE has been registered. The same information is automatically sent to [REDACTED]

The SAE report is reviewed by a designated person at [REDACTED] PV department to ensure that the report is valid and correct. For fatal or life-threatening SAEs where important or relevant information is missing, immediate follow-up is undertaken and queries to the site are raised. Investigators or other site personnel should inform [REDACTED] PV of any follow-up information on a previously reported SAE immediately but no later than the end of the next business day of when he or she becomes aware of it.

If the SAE report in the eCRF is updated, a new e-mail alert is sent to the predefined recipients.

The appointed Medical Monitor will provide his/her causality assessment and make an expectedness assessment once the report is judged to be complete. The reference document for definition of expectedness is the Reference Safety Information (RSI) in the current version of IB.

If any additional documentation is required (e.g. autopsy report), [REDACTED] PV will request this information from the study site.

In case the eCRF cannot be accessed, the SAE should be reported by manually completing the paper SAE Form, provided in the Investigator Site File (ISF). The completed, signed and dated paper SAE Form should, within 24 hours, be scanned or e-mailed to:

A copy of the paper SAE form must also be e-mailed to [REDACTED]

The study site should notify the site Monitor via phone or e-mail about the submission of the SAE report. As soon as the site personnel have access to [REDACTED] the SAE should be reported electronically as well.

The Sponsor has delegated to [REDACTED] the reporting of SAEs to competent authority (CA) and the independent ethics committee (IEC) in accordance with local regulations.

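### AE and SAE collection opens only at IMP application, so a serious harm from the Day 1 local anesthesia or wound punching before dosing has no SAE reporting route

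*Protocol*

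**What the plan says.** The collection window is set in Section 11.7.1.6: "AEs (including SAEs) will be collected from the start of IMP administration until the end-of-study visit". Footnote 22 of Table 8.1-1 (SAD) and footnote 30 of Table 8.1-2 (MAD) repeat it for the Day 1 visit: "From administration of IMP".

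Section 11.3.11 covers the time before that: "A baseline symptom is defined as an event that occurs between subject's signing of the ICF until the first administration of IMP". It glosses this window as the screening period and then rules: "Such events are not AEs and will be recorded as baseline symptoms in the Medical History Log in the eCRF".

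Section 11.7.1.2 defines an SAE as a subset of AEs. Section 11.7.1.12 gives the reporting route: "All available information regarding the SAE should be entered in the AE Log for the specific subject".

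Section 11.4 places the local anesthesia and the 6 mm full-thickness punches on Day 1 before IMP, with one hour (±10%) from the last punch to the start of application. Section 6.3 lists the procedural risks: pain, bleeding, bruising, rare nerve or vessel damage, and anaphylaxis to the local anesthetic, which it describes as very rare. On timing it says: "Any anaphylactic reaction is likely to occur prior to the IMP administration".

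Section 11.7.1.1 makes one provision for pre-treatment procedures. Bleeding and mild, transient inflammation that the investigator attributes to the biopsy are entered in the eCRF as procedure-related; such events become AEs only when judged not procedure-related.

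**The concern.** The volunteers are healthy, gain no medical benefit (Section 6.3), and receive four or eight full-thickness wounds only because they are in the trial. The anesthesia and punching are trial interventions, and the protocol names their risks. Yet the rules sort the resulting events by whether IMP has been applied, not by whether the trial caused them. A serious event an hour before dosing would go into the log that holds prior illnesses, with no seriousness assessment, no 24-hour report and no place in the AE and SAE tables of Section 17.5.1. If that event prevented dosing, the subject would also leave the safety set.

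**Working it through.** No statistical formula applies. The check sets the rules side by side and counts the procedures they affect.

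**1. Procedures before the window opens**

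- Subjects (Section 9.3): 12 in SAD, 24 in MAD.
- Wounds per subject (Section 11.4): 2 per arm in SAD, so 4; 4 per arm in MAD, so 8.
- SAD: 12 × 4 = 48. MAD: 24 × 8 = 192. Total: 48 + 192 = 240 punches in 36 subjects, all made before IMP.

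**2. Length of the interval**

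- Last punch to start of IMP: 60 minutes ± 10%, that is 60 × 0.9 = 54 to 60 × 1.1 = 66 minutes.
- The anesthesia and the earlier punches come before the last punch, so the full interval is longer. The protocol does not fix its total length.

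**3. An anaphylactic reaction to the anesthetic on Day 1, before IMP**

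- Section 11.7.1.6: collection has not opened.
- Section 11.3.11: the event falls between consent and first IMP, so it is a baseline symptom and by rule not an AE.
- Section 11.7.1.2: what is not an AE cannot be an SAE, even if life-threatening.
- Section 11.7.1.12: the report is triggered by saving an AE Log entry as serious. No such entry exists.
- Section 11.7.1.1: the procedure-related entry is limited to bleeding and mild, transient inflammation, so it does not apply. The same holds for a nerve or vessel injury.

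**4. The same reaction at the SAD Day 3 biopsy**

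That biopsy is also done under local anesthesia (Section 11.4), but after IMP. The reaction would be collected as an AE and, if serious, reported as an SAE. The classification depends only on timing relative to IMP.

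**5. Fit of Section 11.3.11 to Day 1**

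The definition runs to first IMP, but its gloss equates this with the screening period. Section 8.1.1 says: "Screening (Visit 1) will take place from Day -28 to Day -1"; Section 8.1.2 says the same for MAD. The Day 1 hours before dosing fit the definition but not the gloss. Both schedules mark the row "Baseline symptoms" only at the screening visit.

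**6. A subject who is never dosed**

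- Both schedules place randomization before wound punching.
- Section 9.8.2.1 allows a randomized but undosed subject to be replaced.
- Section 17.3.1 requires at least one dose for the FAS, which is also the safety set.

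A randomized subject harmed by the anesthesia or punching and therefore not dosed is outside the safety set.

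**The case against.** The strongest reply is that the rule is deliberate and consistent. The primary objective is the safety of activated ILP100-DP, not of the wound model. Opening AE collection at IMP keeps pre-dose events out of the assessment of the product, and Sections 11.3.11 and 11.7.1.6 and both footnotes agree on that point. This stands as a reason to keep the post-IMP tables separate. It is not a reason to leave serious trial-caused events without a reporting route.

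It is also true that pre-IMP events are not simply lost. The Medical History Log is in the eCRF, and Section 17.4.2 has it summarized and listed. Wounds are scored for local tolerability after punching and before IMP. Use of diathermy is noted (Section 11.4). Hemorrhage evident after IMP, persistent exceptional inflammation and any wound infection are AEs (Section 11.7.6.1). Reasons for withdrawal are recorded (Sections 9.2 and 9.8.2). All of this stands and narrows the gap to serious or systemic events with onset before IMP.

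Four stronger readings are tempting but unsupported:

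- **That the protocol expects anaphylaxis.** Section 6.3 calls a true reaction very rare and states only when it would probably occur. Section 9.5 also excludes subjects with known hypersensitivity to local anesthetics.
- **That the 240 punches, or their share of all punches, measure the harms missed.** The count shows which procedures precede the window. An injury from any of them that first appears after IMP is still within collection, and the documents give no rate for acute pre-IMP reactions.
- **That the internal safety review committee would not see such events.** The Principal Investigator is a voting member, Section 8.4.1 provides for rolling review and ad hoc meetings, and the data reviewed are set in a separate charter that is not at hand.
- **That nothing at all is recorded in the Day 1 pre-dose hours because the schedules mark baseline symptoms only at screening.** The definition in Section 11.3.11 does reach to first IMP; the schedule row and the gloss are a wording mismatch.

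**Conclusion.** The point holds in a limited form. Under the protocol as written, a serious reaction to the anesthesia, or a nerve or vessel injury, with onset on Day 1 before IMP is not an AE, cannot be an SAE, and has no reporting route. This applies to the anesthesia and punching session of all 36 planned subjects (240 punches) and the 54 to 66 minutes that follow the last punch. Such an event is improbable, but its consequence would be high: a serious trial-caused harm in a healthy volunteer absent from SAE reporting and the AE and SAE tables and, if dosing did not follow, from the safety set.

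The conclusion assumes that no other document adds a route; the Safety Management Plan and eCRF instructions are not at hand. It does not depend on a statistical analysis plan, because an analysis cannot recover events that were never recorded as AEs. It should be changed because the correction is cheap, not because events are known to be likely.

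**What to change.** Reconcile Sections 11.3.11, 11.7.1.1 and 11.7.1.6 with footnote 22 of Table 8.1-1 and footnote 30 of Table 8.1-2, as follows:

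- Start AE and SAE collection at the first study procedure on Day 1, the local anesthesia.
- Flag events with onset before IMP as pre-IMP/procedure-related, assess them for seriousness, and send serious ones through Section 11.7.1.12.
- Limit Section 11.3.11 to events before that starting point, so that its definition, its gloss and the schedule row agree.
- List pre-IMP events separately for all randomized subjects who underwent anesthesia or punching, including those never dosed. Moving the start of collection alone would leave never-dosed subjects outside the reported set.
- Keep the post-IMP AE tables on the FAS as planned, so attribution to the product is unaffected.

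The cost is protocol and eCRF wording and some additional procedure-related entries.

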#### **11.4 Wound punching/biopsy**

At Visit 2 (Day 1) of each part, standardized full-thickness punch biopsy wounds (6 mm in diameter) will be produced under local anesthesia on the right and left inner arm (2 wounds per arm in the SAD part and 4 wounds per arm in the MAD part).

In the SAD part, one wound punch biopsy per subject will be saved for baseline histology analysis using the procedure described in Section 11.8.2. In addition, on Day 3 of the SAD part, approximately 48 hours after dose, punch biopsies (8 mm) from one wound per arm will be sampled under local anesthesia (injected and/or topical) and saved for histological analysis as described in Section 11.8.2.

Subjects will be treated with local anesthetics (injected and/or topical) in accordance with the manufacturer's instructions and each upper inner arm will be cleaned with 70% ethanol prior to wound incision. The wounds should be placed at least 4 cm apart. Each wound will be labelled with a permanent marker (SAD: L1 to L2 on the left arm, R1 to R2 on the right arm, MAD: L1 to L4 on the left arm and R1 to R4 on the right arm). The position of each number will be the same in all subjects). Subjects will be instructed to fill in the numbering as necessary (at least once weekly up until and including Visit 6 in the SAD part and Visit 13 in the MAD part).

Following wound incision, compression for hemostasis will be applied if necessary. In case of excessive bleeding (which is rare but may occur), where hemostasis is not achieved by compression, diathermy may be used to stop the bleeding. If diathermy is used, this should be noted in the eCRF. The subject may be treated with IMP as planned once hemostasis is achieved. There should be 1 hour ( $\pm 10\%$ ) between the last wound punch and the start of IMP application to allow for pre-dose study assessments and hemostasis. For details on IMP application, refer to Section 10.6. The wound punching procedure will be detailed in a separate manual.

#### **11.5 Wound and Scar Photography**

Photographs of the wounds will be taken prior to IMP application on Day 1 and pre-treatment at all subsequent visits. Each inner arm with 2 to 4 wounds will be photographed separately (i.e. one photo of all wounds, and individual photos of each wound, on the left inner arm and one photo of all wounds on the right inner arm). A self-adhesive ruler, the subject ID, date, time and visit number must be included on each photograph. Photographs should be taken with a high-resolution camera with a macro lens and using standardized lighting (ring flash), using standardized lighting, angle and distance

Details on the camera settings and the photography procedure will be described in a separate manual.

The photographs will be evaluated by 3 to 5 independent evaluators in terms of local tolerability (Section 11.7.6.1), wound healing (Section 11.8.3), wound area (Section 11.8.4) and scar formation (Section 11.8.5).

The photographs will be uploaded in the eCRF.

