### 9.9 Randomization

The randomization in the SAD part of study will be done by arm, i.e. either active treatment to the right arm and placebo to the left arm or vice versa. Each arm will have 2 wounds which will be on same location on both arms.

The randomization in the MAD part of the study will also be done by arm, i.e. active treatment to 4 wounds to the right arm and placebo and saline to 2 wounds each on the left arm or vice versa. The wounds will be placed on the same location on both arms. For details, refer to Table 9.9-1.

A computer-generated randomization list will be created using SAS Proc Plan, SAS Version 9.4. The randomization list will be kept by the randomizer in a sealed envelope until database lock (DBL). A copy of the randomization list will be kept by an unblinded pharmacist at the site.

Sealed individual, treatment code envelopes will be kept in a locked and restricted area at the research clinic in case of need for emergency unblinding and at [REDACTED]

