#### 11.8.4 *Wound area measurements*

The independent evaluators will perform wound area measurements of each wound based on photographs using the Image J software (National Institutes of Health [NIH]) or equivalent at visits specified in (Table 8.1-1 and Table 8.1-2).

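### Section 11.5, as worded, prescribes individual wound photographs on the left arm only; because treatment is randomized by arm, each subject's active and control wounds would have different image sets

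*Protocol*

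**What the plan says.** Protocol Section 11.5 (Wound and Scar Photography) opens with a rule common to both arms: "Each inner arm with 2 to 4 wounds will be photographed separately". A parenthesis then spells the rule out: one photograph of all wounds, and "individual photos of each wound, on the left inner arm and one photo of all wounds on the right inner arm". The section also asks for a high-resolution camera, a macro lens, a ruler in every picture, and standardized lighting, angle and distance. It leaves the details to a separate manual. Sections 8.1.1 and 8.1.2 describe 11.5 as a brief summary of that manual. No other section prescribes individual right-arm photographs with the standard camera.

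Section 9.9 (Randomization) sets the unit of allocation. For the SAD part: "The randomization in the SAD part of study will be done by arm", that is, "either active treatment to the right arm and placebo to the left arm or vice versa". For the MAD part: "The randomization in the MAD part of the study will also be done by arm", with active on the four wounds of one arm and placebo and saline on two wounds each of the other.

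Section 11.8.4 makes photographs the only source of wound area: "The independent evaluators will perform wound area measurements of each wound based on photographs using the Image J software". Section 11.5 adds further uses: "The photographs will be evaluated by 3 to 5 independent evaluators in terms of local tolerability", and also wound healing, wound area and scar formation. Section 17.6.4 plans an active-versus-placebo comparison of the reduction in wound area by ANOVA.

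**The concern.** Active and control wounds always lie on opposite arms, so any difference in how the arms are imaged coincides with treatment within each subject. Section 8.2 presents the subject as his or her own control, which makes this the central comparison. Wound area has no other source, and the photograph-based local reactions belong to the primary endpoints in Section 7.1.1.

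An overview of a whole upper arm shows a 6 mm wound with less edge detail than a close-up does. The ruler calibrates scale but does not restore detail, and detail matters more as the wound shrinks. Right-arm close-ups that are not taken at a visit cannot be recovered later.

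**Working it through.** The plan states no figure to reproduce. The check has a textual part and two supporting calculations.

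**Text.** The parenthesis in 11.5 explains the opening rule and lists two photograph types for the left arm but one for the right. Sections 8.1.1 and 8.1.2 say only that wounds are photographed in a standardized setting according to the manual. Neither they nor Sections 11.7.6.1, 11.8.3, 11.8.4 and 11.8.5 say which image type the evaluators use.

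**Field of view.** Inputs: wound diameter 0.6 cm and spacing of at least 4 cm (Section 11.4); 2 wounds per arm in SAD and 4 in MAD. With 4 cm between centres, the smallest span for k wounds is 0.6 + 4(k − 1) cm:

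- SAD: 0.6 + 4 = 4.6 cm
- MAD: 0.6 + 12 = 12.6 cm

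If the 4 cm runs edge to edge, the span is 0.6k + 4(k − 1): 5.2 cm in SAD and 14.4 cm in MAD.

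The field of a close-up is not given; I assume 2 to 5 cm on the same sensor. The ratio of linear resolution is overview span divided by close-up field. For centre-to-centre spacing:

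| Close-up field (assumed) | SAD, 4.6 cm | MAD, 12.6 cm |
|---|---|---|
| 2 cm | 2.3 | 6.3 |
| 3 cm | 1.5 | 4.2 |
| 5 cm | 0.9 | 2.5 |

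The overview is therefore about 2.5 to 6.3 times coarser in MAD. In SAD it runs from about equal to 2.3 times coarser.

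**Effect on the contrast.** Let d be the left-minus-right measurement difference. It enters a subject's active-minus-control contrast as +d if active is on the left and −d if it is on the right. The cohort mean is shifted by d(nL − nR)/n, where nL and nR count subjects with active on the left and right.

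- Balanced sides: the shift is 0, but each contrast still moves by ±d, which adds d² to its variance.
- Cohort of 4: a 3:1 split shifts the mean by d/2, and a 4:0 split by d.
- Cohort of 8: a 5:3 split shifts it by d/4.

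**Chance of imbalance.** The text of Section 9.9 does not say whether sides are balanced within a cohort. Under simple 1:1 allocation (assumption):

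- n = 4: P(unequal) = 1 − 6/16 = 0.625; P(all on one side) = 2/16 = 0.125
- n = 8: P(unequal) = 1 − 70/256 = 0.727

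Under allocation balanced within cohort, P(unequal) is 0 at randomization. The MAD example in Table 9.9-1 has active on the right, right, left and left for its four sequences, a 2:2 split. That suggests balance but does not establish it.

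**The case against.** The strongest reply is that this is a wording slip and not a plan to image the arms differently. The sentence begins with both arms alike, the reference to individual photographs looks like an insertion made on one side only, and the section demands a standardized angle and distance. The governing instruction is the manual, which may well prescribe the same set for both arms. This stands as to intent. It does not remove the asymmetry from the protocol text, and if the manual is symmetric the two documents disagree.

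Second, a reader might infer that one treatment is necessarily measured from close-ups and the other from a wide shot. The documents do not support that, because they do not name the image used. If evaluators used the overview on both arms, image quality would be equal.

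Third, wound area is analysed as reduction from a baseline photograph (Section 7.2.1; footnotes to Tables 8.1-1 and 8.1-2). If each arm is imaged the same way throughout, a constant left/right offset largely cancels. This stands, and leaves mainly noise.

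Fourth, coarser resolution is not itself measurement error. If one assumes 4000 to 6000 pixels across 14 cm, a 6 mm wound still spans about 170 to 260 pixels (0.6/14 of the width). The documents give no basis for converting this into an error in area or ratings.

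Finally, exposure is limited. The investigator assesses tolerability, healing, rupture and scar directly on both arms. Long-term tolerability and scar are rated by the investigator alone, and the 3D camera images each wound. This stands, but wound area from standard photographs has no direct-observation counterpart, and 3D imaging is exploratory.

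**Conclusion.** The point holds in a limited form. Section 11.5 as worded gives the arms different photograph sets, nothing else in the protocol corrects it, and arm is the unit of randomization. Following the text would give every subject's active and control wounds different image sets.

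The consequence depends on evaluators using close-ups where available, which is not stated. On that assumption the main effect is avoidable noise in the within-subject contrast, larger in MAD than in SAD. The resolution ratios rest on the assumed close-up field of 2 to 5 cm, and the size of d is unknown.

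A reader might also infer a systematic advantage or disadvantage for active treatment. The documents do not support this: the side is randomized, so the difference averages out over allocations. Bias in a given cohort needs unbalanced sides, whether from simple allocation or from withdrawals or missing photographs. The imbalance probabilities of 0.625 and 0.727 should not be taken as properties of this trial, since they require simple allocation and the only example shown is side-balanced.

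The correction is still more than clerical, because the sentence is a data-collection rule.

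**What to change.** Reword Section 11.5 so that each inner arm gets one photograph of all its wounds and an individual photograph of each wound, with the same distance and settings. State that the independent evaluators use the same image type for both arms, and name which type serves for wound area and which for the ratings. Check the photography manual and bring it into line.

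The cost is a sentence or two in the protocol, a check of the manual, and up to 2 (SAD) or 4 (MAD) extra frames per visit for the right-arm wounds. No dose, schedule or clinical rule is touched.
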